## Discussion

Primarily driven by individuals with DCM, word clouds were developed for associations with the diagnosis, treatment, long-term phases of care, and an “other” category. These will be nested within AO Spine RECODE-DCM, in order to evaluate their role in supporting the research uncertainty gathering phase of a JLA Research Priority Setting Partnership.

The diagnosis word cloud highlights prominent symptoms and MRI, the gold standard diagnostic tool. The treatment section highlighted the gold standard treatment—surgical decompression. The long-term management section highlighted disability and tiredness. The other category highlighted ignorance of the condition. Amongst several pervasive themes were pain and psychological consequences such as anxiety and depression.

The perspective of PwCM has been limited within DCM research to date, but wider experience from healthcare shows this can bring critical insights [8]. In one of the few previous DCM examples, our evaluation of PwCM recovery priorities identified that pain, alongside upper and lower limb function, was most valued [18]. This contrasts the current outcomes of research studies not including PwCM input and supports the rationale for AO Spine RECODE-DCM, and its establishment of a minimum data set. The broad range of ideas displayed goes beyond current research foci [23] indicating the value of engaging PwCM in research design [8].

We hypothesize that this PwCM perspective could be enhanced within a JLA PSP. While PSP were developed to ensure the voice of patients is incorporated into setting a research agenda, this is only really considered by the group as a whole during the final consensus meeting. Put specifically, professionals do not have the opportunity to reflect on “patient” perspectives until summary questions have already been generated and shortlisted. In this nested methodological study, we will therefore evaluate whether the PwCM generated word clouds can help the group as a whole develop research questions and specifically, priority research questions.

Word clouds are a clustering technique mainly applied for the visual analysis of qualitative data. A search of MEDLINE for “Wordcloud” or “Word Cloud,” including title and abstract screening, returned 53 articles (12 August 2019). Articles describe word cloud use to depict survey, workshop/forum, or medical literature data as well as other interesting applications to assist keyword identification for literature searches [24, 25] and to evaluate reference letters for residency programs [26]. There are currently only two references to their use for stimulating ideas and both were deemed effective; first in palliative care, where word clouds were generated by a palliative patient and their family, to support positive memories during the bereavement process [27], and secondly, as part of an education initiative asking medical students to consider “What is professionalism?” [28]. Word cloud usage outside of medicine is much broader [16].

The methodology to form the word clouds was developed by the management group of AO Spine RECODE-DCM. Only a single prior study evaluating the design of word clouds was identified, in which the semantic grouping of word clouds was found to be more effective [15]. In the DCM context, word clouds for each section (diagnosis, treatment, etc.) were derived as opposed to a single word cloud for all DCM concepts. This was chosen to match the predefined questions covering phases of care, and in line with our principal objective to encourage broader research uncertainty gathering. Additionally, a two-stage development process was used, whereby ideas were gathered before being represented to the group for polling. Whether a two-stage development process was required is unclear. It was partly inspired by the two-stage iterative processes that are common to most DELPHI processes. However, it may be more efficient to generate a provisional list internally and then simply develop a poll where users can make additional suggestions. Of note, while unmeasurable, it was our sense that the two-stage process helped to focus the community to the task and its objectives in this instance.

We acknowledge that this was an internet-recruited, convenience sample of persons with DCM. Therefore, the generalization of these word clouds, in the absence of demographics, cannot be fully evaluated. Experience from prior research involving this group indicates their demographics and disease characteristics are broadly representative of DCM [18–22]; moreover, the use of such sampling is the mainstay of traditional JLA PSP [29]. As these details will be captured within AO Spine RECODE-DCM, potential bias can be evaluated.

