## Methods

The word clouds were generated working with Myelopathy Support, an online peer-to-peer support community for individuals with DCM and their caregivers. Ethical approval has not been required for the involvement of the Myelopathy Support members as their role is to help to develop the word clouds for the survey and they are not research participants. The moderator for the Myelopathy Support group is a member of the Steering Group for the Priority Setting Partnership who design and manage the survey. Myelopathy Support is an arm of Myelopathy.org, an international charity for DCM. Myelopathy Support includes an online support group hosted on Facebook (California, USA). The group is closed, and access is moderated by Myelopathy.org volunteers [IS]. Individuals wishing to join the group are required to confirm they have myelopathy and will adhere to community guidelines. Prior experience has demonstrated that demographics and disease characteristics of this group, aside from a female gender predominance, are broadly representative of DCM [18–22].

Over a 2-week period, four posts were pinned to the top of the Myelopathy Support group: (1) “What words do you associate with diagnosis phase of myelopathy?” (2) “What words do you associate with the management phase of myelopathy?” (3) “What words do you associate with the long-term care/living with myelopathy?” (4) “Any other relevant words?”. The posts were accompanied by covering information outlining the background and rationale for this exercise, piloted and approved by IS [Supporting Information 1]. In short, group members were encouraged to add their unrepresented suggestions as comments on the particular post or posts and to vote (as likes or with emotions) the posted words with which they agreed. This exercise was moderated by a group administrator [IS]. No data was collected on individual participants, e.g., their demographics. There was no limit on how many times a group member could contribute.

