## Implementation plan for AO Spine RECODE-DCM

AO Spine RECODE-DCM includes several parallel consensus processes, including a research priority setting partnership and the development of a minimum data set. The AO Spine RECODE-DCM survey will be accessed via a single-entry point, with block randomization to one of the two streams (either Priority Setting Partnership or Minimum Data Set) per stakeholder group (spinal surgeon, other healthcare professionals, persons with DCM and their supporters). This methodology was chosen for efficiency to enable a single recruitment phase. Further detail on the overall process is provided in reference [5].

For participants allocated to the PSP, further 1:1 block randomization will occur to two streams, a survey including word clouds and a second stream without word clouds. For those allocated to the word cloud stream, participants will complete the survey as planned initially. However, after survey completion, respondents will be presented with a brief overview of the development method and aims of the word cloud subproject. Participants will then be presented with each word cloud in turn, with the option to submit further research questions. This approach was taken for two principal reasons. Firstly, to ensure the traditional JLA methodology can be conducted contemporaneously, but still partitioned if required, and secondly, to enable any cross over of responses within the word cloud arm to be considered. Participants will be able to move freely within the survey up until the point they reached a final “thank you” page. Consequently, it will be theoretically possible for participants in the word cloud stream to edit their pre-word cloud form having seen the word clouds. This cannot be tracked by the survey platform. However, by retaining an arm who have no access to the word clouds, any such cross over can be evaluated.

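### Survey demographics cannot show whether the word cloud contributors were representative: the article reports no data on them and describes no link between them and survey respondents

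*Protocol article*

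**What the plan says.** The word clouds were built from two rounds of posts and polls in an online support group. The Methods section of the Protocol article describes the contributors in these terms:

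- On their status: "their role is to help to develop the word clouds for the survey and they are not research participants".
- On what was recorded about them: "No data was collected on individual participants, e.g., their demographics".
- On the first round: "There was no limit on how many times a group member could contribute". In the second round, members could vote only once.

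The limitations paragraph of the Discussion begins "We acknowledge that this was an internet-recruited, convenience sample of persons with DCM" and continues "Therefore, the generalization of these word clouds, in the absence of demographics, cannot be fully evaluated". It then cites earlier research in the same group and the usual sampling practice of priority setting partnerships, and ends with "As these details will be captured within AO Spine RECODE-DCM, potential bias can be evaluated".

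The implementation plan describes the later survey: "The AO Spine RECODE-DCM survey will be accessed via a single-entry point, with block randomization to one of the two streams". Allocation is done within stakeholder groups. Those allocated to the Priority Setting Partnership (PSP) are then randomized 1:1 to a survey with or without word clouds.

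**The concern.** The limitation and its proposed remedy concern different people. The limitation is about those who suggested and voted on words. The details captured within AO Spine RECODE-DCM would be those of people who answer the survey. Some individuals may belong to both sets, but the article describes nothing that would identify them.

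Two things are at stake. First, a reader could take the closing sentence as assurance that the representativeness of the clouds will be checked, when the described data do not allow it. Second, and less important, people with DCM who worked through the word lists may later answer the survey, and randomization would place them in both PSP streams. Those in the stream without clouds would already know the words, which could reduce the stream difference in that stakeholder group.

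**Working it through.** The plan gives no figure here to reproduce and no arithmetic applies. The check is whether the stated property follows from the data described.

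**Step 1: what an evaluation of bias needs.** It needs (a) the characteristics of the people who contributed words and votes, (b) the characteristics of a reference population, and (c) a comparison of the two.

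**Step 2: what the survey supplies.** The Discussion says these details will be captured in RECODE-DCM. That gives a description of survey respondents, which could serve as (b).

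**Step 3: whether (a) can be obtained.**

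- *Directly:* no. The Methods say nothing was collected on individuals.
- *From the word and vote counts:* no. The Results report 79 words submitted in the first round, but contributions were unlimited, so this does not even give the number of contributors. The highest second-round count, 47 votes for one word, is a tally and says nothing about who voted.
- *Through the survey:* only if poll contributors can be recognised among respondents. The article describes no identifier and no question on poll participation.
- *From earlier studies of the group:* only indirectly. They describe the group in general, not the self-selected members who took part in these polls. The Methods also note a female predominance as an exception, which the Discussion does not repeat.

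**Step 4: result.** With (b) but not (a), comparison (c) cannot be made. The closing sentence therefore claims more than the described design supports.

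**Step 5: consequence for the stream comparison.** Prior contributors who reach the PSP are randomized like everyone else, so they are balanced between streams in expectation and the comparison stays valid. If the clouds do less for people who already know the words, the difference among people with DCM would be smaller than among those new to them. It would reach the overall figure only through that group's share. Sizing this needs the number of prior contributors who join, the number of people with DCM in the PSP, and the effect of the clouds on those already exposed. The documents give none of the three.

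**The case against.** **The sentence may mean something else.** The clause before it is about sampling in priority setting partnerships generally. The sentence could therefore refer to bias in the survey sample, which survey demographics can address. That reading is possible. But the paragraph's subject is the convenience sample behind the clouds, and the missing details are that sample's demographics. If survey-sample bias is meant, the sentence should say so.

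**The limitation is already disclosed.** The paragraph itself says that generalization, "in the absence of demographics, cannot be fully evaluated". This stands and narrows the point: the fault is a closing sentence that goes beyond the concession made just before it.

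**The article is condensed.** The questionnaire is not shown, and further detail is referred to a cited publication. One can therefore say only that the article describes no link, not that none exists. But no fuller document can restore data that the Methods say were not collected.

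**Stronger readings a reader might infer.**

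- *That prior exposure undermines the randomized comparison.* The documents do not support this. Exposure is balanced by allocation, and any dilution arises only among people with DCM. The hypothesis in the Abstract and Introduction concerns other stakeholders, and the metrics are also reported per stakeholder group.
- *That the dilution can be quantified.* One could start from 47 votes, assume that 25% to 100% of those voters join and half go to the PSP, and obtain 47 × 0.25 ÷ 2 = 5.9 to 47 × 1 ÷ 2 = 23.5 people. That is 6% to 24% of an assumed 100 people with DCM in the PSP, or 3% to 12% of an assumed 200. The uptake and both denominators are invented, the vote count may include merged duplicates, and equating these shares with dilution assumes that the clouds do nothing for people who know the words. Yet the cloud stream gives everyone a further chance to submit questions. These figures should not be relied on.

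**Conclusion.** The point holds in a limited form. On its natural reading, the claim that bias in the word cloud sample can be evaluated does not follow from the described design. Survey demographics can describe respondents or act as a reference, but cannot show whether contributors were representative. This rests on the explicit statement in the Methods that no individual data were collected, and on the absence from the article of any described link.

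The consequence is mainly one of interpretation. The randomized comparison remains valid, and comparisons among healthcare professionals are not affected. Some dilution among people with DCM is plausible, but the documents give no basis for its size.

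**What to change.** For people with DCM, add one yes/no item among the entry or demographic questions, **before randomization**, asking whether the respondent suggested or voted on words in the Myelopathy Support polls. Allocation is done per stakeholder group, so the group must already be known at that stage and the item can sit beside it. Use it in two ways:

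1. Compare the characteristics of prior contributors and non-contributors among respondents with DCM.
2. As a sensitivity analysis, repeat the stream comparison in people with DCM without the prior contributors.

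Do not ask at the end of the survey whether respondents have seen the clouds. By then everyone in the cloud stream who has gone through the survey has just been shown them. Answers would differ by stream, and exclusions based on them could bias the comparison. An answer given before randomization cannot be influenced by allocation.

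The cost is one question and one additional analysis. The item relies on recall and reaches only contributors who join the survey, so the evidence on representativeness would be partial and should be reported as such.

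If the item cannot be added, limit the closing sentence to bias in the survey sample and leave the concession about the word clouds as it stands. That costs one edited sentence.

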## Conclusion

We have shown it is feasible to work with PwCM with relevant experience to generate a tool for the AO Spine RECODE-DCM nested methodological study. Once the survey stage is completed, we will be able to evaluate the impact of the word clouds. Further research will be needed to assess the value of any impact in terms of stimulating a more creative research agenda.

## Data Availability

The datasets used and/or analyzed during the current study are available from the corresponding author on reasonable request.
